### Determination of sample size

The sample size calculation was derived from the primary endpoint, based on patients with none of the three individual outcomes: major congenital malformations, perinatal death or neonatal death. The probability of this combination of endpoints is not known within the literature. However, based on data from a UK population study [10], which are in line with results from other European countries [1, 2, 4, 11–13], the proportion of pregnancies with any of the above outcomes is estimated at 8.2%: major congenital malformations, 4.5%; perinatal death, 3%; neonatal death, 0.9% (8.2% is computed under the assumption that the individual outcomes are independent). The proportion of pregnancies *without* any of the above outcomes is therefore estimated at 91.8%.

The goal is to be able to detect a difference of 3.5% between the proportions without the combined endpoint in the IDet group compared with the other basal insulin regimens group. Assuming a maximum 1:2 split between the two groups (IDet group: other basal insulin regimens group), a sample size of 1833 pregnancies is needed to have 80% power of achieving significance at a 5% level.

To achieve a total of 1833 pregnancies for the assessment of the primary endpoint, the planned number of patients to be included during the 5 years of the recruitment period is 3075. This number is based on the expectation that ~20% of pregnancies will result in a spontaneous abortion, ~10% will be treated with other antidiabetic injectables or will change basal insulin treatment and ~10% will be lost to follow-up, leaving 60% of pregnancies (i.e., 1833) assessable for the primary endpoint.

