**Methods:**

The present study is a prospective, non-interventional, multicentre cohort study conducted in seven countries, designed to assess the safety of insulin detemir during pregnancy, and to monitor the health status of resulting infants (exposed in utero) up to 1 year of age. The study population includes women with type 1 or type 2 diabetes, who are pregnant and being treated with insulin. Data will be collected in the context of routine practice. The primary endpoint is the proportion of pregnancies in women treated with insulin detemir, compared with other basal insulin regimens, which do not result in any of the following events: major congenital malformations, perinatal death or neonatal death. A sample size of 3075 pregnancies was calculated to provide an 80% power to detect a difference of 3.5% between groups in the primary endpoint at a 5% level.

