### Statistical considerations

The analysis set will consist of all pregnancies among patients who are treated with basal insulin and have not changed basal insulin product for 4 weeks prior to conception and during pregnancy. Continuous variables will be summarised with descriptive statistics, and categorical variables will be displayed in frequency tables.

The primary endpoint will be analysed using a logistic regression model that will include treatment group, study site, race, hypertension, major hypoglycaemic events during pregnancy, folic acid intake and use of GLP-1 agonists during pregnancy as factors. HbA_1c_ at the start of pregnancy, the end of the first trimester and the end of the second trimester, age and body mass index at baseline, duration of diabetes, blood pressure and previous perinatal complications will be included as covariates. The primary endpoint will be computed for the IDet group and for the ‘other basal insulin’ group and the absolute difference between these proportions calculated, along with the 95% CI and the *p*-value using Fisher’s exact test.

For infant endpoints at 1 year, the proportions will also be analysed using logistic regression. Factors and covariates will be as per the primary endpoint. Analyses regarding height and weight will also be adjusted for exclusive and/or partial lactation period. Similar analyses will be performed for all other endpoints that are proportions.

Means of the continuous endpoints will be compared between the two groups using an analysis of covariance model.

The incidence of major hypoglycaemia during pregnancy will be computed for both treatment groups.

Observations of possible clinical importance (such as the primary endpoint split out according to diabetes type, insulin analogue or use of an insulin pump) will be presented using descriptive statistics.

All statistical analyses will be performed using appropriate statistical software, and tests will be performed as two-sided tests with a significance level of 0.05.

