The very liberal inclusion and exclusion criteria of this study mean that the population will be largely unselected, as compared with the highly selected populations typically eligible for RCTs. The results will therefore be more broadly applicable to the real-world population of pregnant women with diabetes. Furthermore, as the study collects data based on standard routine care, participation will be substantially less demanding on the women recruited, as compared with RCTs.

In summary, this is an international, prospective, non-interventional, multicentre, cohort study designed to assess the safety of IDet in comparison with other types of insulin treatment during pregnancy, and to monitor the health status of the resulting infants - who were exposed in utero - up to 1 year of age. The planned enrolment of 3075 patients is sufficiently large to allow comparison of the frequency of rare events, such as congenital malformations and perinatal/neonatal death, between the various insulin treatment regimens. The study will therefore provide valuable information on these events, as well as other relevant maternal, pregnancy and infant-related endpoints, to inform future prescribing with basal insulins in diabetic pregnancy.

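### The direction-free claim of 80% power for a 3.5-point difference holds only if 91.8% event-free is the lower proportion; if it is the comparator rate and detemir is 3.5 points worse, power is about 65%

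*Protocol article*

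**What the plan says.** All the inputs are in the protocol article.

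- **Base rate (Determination of sample size).** The share of pregnancies with any of the three outcomes "is estimated at 8.2%: major congenital malformations, 4.5%; perinatal death, 3%; neonatal death, 0.9" per cent, combined as if independent. The event-free proportion is therefore 91.8%. It comes from population data and is not assigned to either treatment group.
- **Target (same section).** "The goal is to be able to detect a difference of 3.5% between the proportions without the combined endpoint in the IDet group". The contrast is against women on any other basal insulin, and no direction is given.
- **Allocation (same section).** "Assuming a maximum 1:2 split between the two groups (IDet group: other basal insulin regimens group").
- **Claim (same section).** "a sample size of 1833 pregnancies is needed to have 80% power of achieving significance at a 5% level".
- **Claim in the Abstract, Methods.** "A sample size of 3075 pregnancies was calculated to provide an 80% power to detect a difference of 3.5% between groups". Again there is no direction, and the power is attached to the enrolment figure.
- **Test (Statistical considerations).** The absolute difference in proportions is reported with a 95% CI and a p-value from Fisher's exact test, and "tests will be performed as two-sided tests with a significance level of 0.05". An adjusted logistic regression is also planned for the primary endpoint.

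**The concern.** Near 92%, the variance of a proportion changes quickly. A gap of 3.5 points is easier to detect when the second group is at 95.3% than when it is at 88.3%. A power statement for a 3.5-point difference under a two-sided test, with one base rate and no direction, covers both cases, and one sample size cannot give 80% in both.

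The difference matters because of the study's purpose. The Background section describes a post-authorisation safety study requested by the regulator, and the design section says that it will assess the safety of detemir. A result in which detemir does worse than the background rate is one the study exists to find. A reader of the abstract would take the chance of missing a 3.5-point harm to be one in five. If the comparator is at the literature rate, it is closer to one in three.

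**Working it through.** **Inputs.** Two-sided alpha 0.05. Of 1833 pregnancies split 1:2, 611 are on detemir and 1222 on other basal insulins. Difference d = 0.035. The base event rate is checked first: 1 − 0.955 × 0.970 × 0.991 = 0.082, so 91.8% event-free is right.

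**Formula (pooled normal approximation).** With event rates p1 (detemir) and p2 (other) and p̄ = (p1 + 2·p2)/3:

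- s0 = √[p̄(1 − p̄)(1/611 + 1/1222)]
- s1 = √[p1(1 − p1)/611 + p2(1 − p2)/1222]
- power = Φ[(d − 1.96·s0)/s1]

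Exact power of the two-sided Fisher test was also computed by summing the binomial probabilities of all outcomes with p ≤ 0.05.

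**Step 1: reproduce the stated figure.** Detemir 4.7% events, other 8.2% (95.3% against 91.8% event-free):

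- p̄ = 0.0703, s0 = 0.01267, s1 = 0.01162
- (0.035 − 0.02483)/0.01162 = 0.875, so power = 80.9%; Fisher 80.3%
- The pooled formula asks for 598 on detemir, a total of 1794, about 2% below 1833.

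With the groups exchanged (detemir 8.2%, other 4.7%), the continuity-corrected formula gives a total of 1803, and Fisher power at 1833 is 82.0%. The plan's figure is thus reproduced to within 3% when 91.8% is the lower event-free proportion.

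**Step 2: same sample, detemir worse than a comparator at 91.8%.** Detemir 11.7% events, other 8.2% (88.3% against 91.8%):

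- p̄ = 0.0937, s0 = 0.01444, s1 = 0.01519
- (0.035 − 0.02829)/0.01519 = 0.4415, so power = 67.1%; Fisher 65.2%
- Other approximations: continuity-corrected 64.1%, unpooled 63.5%, arcsine 65.9%. The shortfall does not depend on the method.

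**Step 3: all placements of 91.8%, at 611:1222.**

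| Event-free, detemir | Event-free, other | Fisher power | Pooled normal |
|---|---|---|---|
| 95.3% | 91.8% | 80.3% | 80.9% |
| 91.8% | 95.3% | 82.0% | 83.2% |
| 93.55% | 90.05% | 71.1% | 71.7% |
| 90.05% | 93.55% | 72.8% | 74.5% |
| 88.3% | 91.8% | 65.2% | 67.1% |
| 91.8% | 88.3% | 63.5% | 64.1% |

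What drives the result is whether 91.8% is the lower, middle or higher value. Which group is the better one matters little.

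**Step 4: what 1833 can detect, and what a 3.5-point worsening would need.** With the comparator at 8.2% events, Fisher power is 79.5% for a rise of 4.2 points and 81.2% for a rise of 4.3 points. For 80% power against 11.7% versus 8.2%, the pooled formula needs 842 on detemir, a total of 2526; the continuity-corrected formula needs 2652 (Fisher power there 80.8%). At the planned 60% assessable, that is 2526/0.6 = 4210 to 2652/0.6 = 4420 enrolled. These totals show the size of the gap and are not a proposal.

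**The case against.** **The calculation is not wrong.** The article's 80% is met under a reading consistent with its inputs, so the fault is an unstated alternative and not bad arithmetic. This stands. The full protocol may also name the alternative. That would not repair the published sentences, which claim 80% for a difference in either direction.

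**It is not simply benefit against harm.** A reader might infer that the 80% belongs to the benefit direction and that power is 65% whenever detemir is worse. The figures do not support that. Detemir worse at 91.8% against 95.3% has 82.0% power; detemir better at 91.8% against 88.3% has only 63.5%. The article never assigns 91.8% to the comparator. Using a population rate as the comparator rate is reasonable, but it is an assumption, and the 65% depends on it.

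**No passage plans to conclude safety from a non-significant test.** This also stands. The primary objective is worded as estimation, and the 95% CI of the difference would show whether a 3.5-point harm had been excluded. A reader might fear false reassurance, but the document does not set up that inference.

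**The Discussion is not contradicted.** Its sentence "The planned enrolment of 3075 patients is sufficiently large to allow comparison of the frequency of rare events" states no power, direction or margin, so these figures do not refute it.

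**Allocation could be kinder.** The article treats 1:2 as the maximum imbalance and says that sites prescribe detemir relatively often. At 1:1, Fisher power for 88.3% against 91.8% would be about 71%, still short of 80%.

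**Conclusion.** The concern holds in conditional form. The unqualified 80% in the Abstract and in Determination of sample size is correct only if 91.8% is the lower event-free proportion. If the comparator is at 91.8% and detemir is 3.5 points worse, power is about 65% by the planned Fisher test, and 63.5% to 67.1% across methods. With the difference centred on 91.8%, it is about 71% to 73%.

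This rests on 1833 assessable pregnancies, a 1:2 split, a two-sided 5% level and the unadjusted comparison of proportions. The adjusted logistic model was not evaluated. The point should be fixed because readers of a regulator-requested safety study will rely on the figure, but it does not invalidate the design or the sample size.

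**What to change.** In Determination of sample size, state which group is assumed at 91.8% and what proportion is assumed in the other. If 91.8% is meant as the comparator rate, the power statement could read:

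> With 1833 assessable pregnancies (1:2) and 91.8% event-free in the comparator, the unadjusted two-sided comparison has 80% power for a 3.5-point improvement with detemir, about 65% for a 3.5-point worsening, and 80% for a worsening of about 4.2 to 4.3 points.

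Bring the Abstract into line, attaching the power to the assessable pregnancies and giving the direction. The Discussion needs nothing beyond consistency with this.

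The cost is a few sentences and a less favourable stated figure. Enrolment, test and analysis stay as they are.

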Major hypoglycaemia	A hypoglycaemic episode in which the patient is not able to treat themselves and in which oral carbohydrates, glucagon or intravenous glucose has to be administered to the patient by another person because of severe central nervous system dysfunction
Neonatal death	Death of an infant between 7 and 28 completed days after delivery
Perinatal death	Death of a foetus/infant at ≥22 completed gestational weeks and <1 completed week after delivery
Preterm delivery	Delivery before 37 completed gestational weeks
Pre-eclampsia	A condition in pregnancy characterised by new onset of abrupt hypertension (≥140/90 mmHg documented on two occasions, ≥6 h and ≤7 days apart) and proteinuria/albuminuria
Spontaneous abortion	A naturally occurring termination of a pregnancy before 22 completed gestation weeks

The study has a fixed recruitment period of 5 years (September 2013 to September 2018), and will include gestation and follow-up of infants at 1 month and 1 year of age. The planned enrolment is 3055 patients.

The study population will include women with T1D or T2D (as assessed from maternal medical history) who are pregnant and being treated with insulin or other injectable antidiabetic treatment regimens, and who have not changed their basal insulin or other injectable antidiabetic treatment for 4 weeks prior to and following conception. Inclusion and exclusion criteria are listed in Table 2.

**Table 2 Tab2:** Inclusion and exclusion criteria

Inclusion criteria
• Woman with a positive pregnancy test
• Type 1 diabetes or type 2 diabetes, diagnosed prior to conception
• Treated with unchanged basal insulin or other injectable antidiabetic treatment (for those not treated with basal insulin) for 4 weeks prior to and following conception
• Informed consent obtained before any data collection
Exclusion criteria
• Women who have been pregnant for >12 weeks at baseline visit confirmed by ultrasound

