### Study organisation

The study is being conducted across approximately 53 study sites in 14 countries. The anticipated numbers of patients per country are as follows: Croatia, 355; Denmark, 620; Finland, 100; France, 150; Germany, 135; Israel, 350; Italy, 130; Netherlands, 100; Poland, 200; Romania, 60; Spain, 375; and UK, 300. Additional countries and study sites might be included during the study period. Sites have relatively similar standard routine procedures with regard to the treatment of women with diabetes during pregnancy and have a relatively high prescription rate of IDet. The projected study timeline is given in Fig. 2.

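### Planned enrolment is stated as both 3055 and 3075, the derivation gives 3055, and the country list sums to 2875 over 12 of a stated 14 countries

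*Protocol article*

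**What the plan says.** Enrolment is given in four places in the protocol article.

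- Methods/design: "The planned enrolment is 3055 patients".
- Determination of sample size: "the planned number of patients to be included during the 5 years of the recruitment period is 3075".
- Abstract, Methods: "A sample size of 3075 pregnancies was calculated to provide an 80% power to detect a difference of 3.5% between groups".
- Discussion, closing paragraph: "The planned enrolment of 3075 patients is sufficiently large".

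The sample-size section first sets the number to be analysed: "a sample size of 1833 pregnancies is needed to have 80% power of achieving significance at a 5% level". It then allows for losses of roughly 20% (spontaneous abortion), 10% (other injectables or a change of basal insulin) and 10% (loss to follow-up). It concludes that 60% remain, and it equates that 60% with 1833.

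On geography, Study organisation states: "The study is being conducted across approximately 53 study sites in 14 countries". It then gives an anticipated number for each named country, ending with "Romania, 60; Spain, 375; and UK, 300", and adds that further countries and sites may join. The abstract describes a "multicentre cohort study conducted in seven countries".

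**The concern.** The article carries two enrolment figures and does not explain the difference. The one printed in the sample-size section is not the one that section's own calculation produces. The country numbers add to neither, and three different country counts (seven, 12 and 14) can be read from the text.

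The abstract adds a further slip. It attaches the 80% power to the enrolled number, whereas the sample-size section attaches it to the 1833 pregnancies left after losses.

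This is a safety study requested by a regulator. Its recruitment will be judged against the stated target, and a reader could take 3055, 3075 or 2875 as the plan.

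**Working it through.** **Inputs.** From Determination of sample size: 1833 assessable pregnancies; losses of about 20%, 10% and 10%; 91.8% event-free; a difference of 3.5 percentage points; a 1:2 split (IDet : other basal insulin). From Statistical considerations: two-sided 5% level. From Study organisation: the country numbers.

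**1. The plan's 1833.** Standard two-proportion formula, 80% power, 1:2 split, 91.8% against 95.3%:
- IDet at 95.3%, no continuity correction: total 1793.
- IDet at 91.8%, with continuity correction: total 1803.

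Both lie within 3% of 1833 (40/1833 = 2.2%; 30/1833 = 1.6%), so 1833 is taken as given.

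**2. From assessable to enrolled.**
- Assessable share = 1 − 0.20 − 0.10 − 0.10 = 0.60.
- Enrolment = 1833 / 0.60 = 3055, the Methods/design figure exactly.
- In reverse, 0.60 × 3075 = 1845, not 1833.
- 1833 / 3075 = 59.6%.
- Applying the losses in sequence does not give 3075 either: 0.8 × 0.9 × 0.9 = 0.648, and 1833 / 0.648 ≈ 2829.
- Gap between the stated figures: 3075 − 3055 = 20, and 20/3055 = 0.65%.

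**3. The country numbers.** In the order printed:

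355 + 620 + 100 + 150 + 135 + 350 + 130 + 100 + 200 + 60 + 375 + 300 = 2875, over 12 countries.

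- 3055 − 2875 = 180.
- 3075 − 2875 = 200.
- 14 − 12 = 2 countries counted but not listed.

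**4. What the listed countries alone would yield.** 0.60 × 2875 = 1725 assessable, which is 1833 − 1725 = 108 fewer (5.9%).

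**5. Power at 1725 and 1833.** Take IDet at 95.3% and the comparator at 91.8%, with no continuity correction. The pooled proportion is (0.953 + 2 × 0.918)/3 = 0.9297. Power = Φ[(0.035 − 1.96 × SE₀)/SE₁], with SE₀ the pooled and SE₁ the unpooled standard error.

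| Assessable | Groups | SE₀ | SE₁ | Power |
|---|---|---|---|---|
| 1833 | 611 : 1222 | 0.01267 | 0.01162 | 80.9% |
| 1725 | 575 : 1150 | 0.01306 | 0.01197 | 78.4% |

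With the percentages the other way round (IDet 91.8%, comparator 95.3%), power is 83.2% at 1833 and 81.1% at 1725. At 1845, the yield from 3075, power in the tabulated case is 81.2%.

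**The case against.** **The loss rates are approximate.** All three are marked as approximate, and 1833/3075 = 59.6% rounds to 60%. So 3075 is compatible with the derivation at its stated precision. It is also the figure given in three of four places, and it could be the approved target with a small margin. This stands in part: the article does not settle which figure is in force, so 3055 should not be imposed. It does not explain why the exact quotient is printed elsewhere as the planned enrolment.

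**Twenty patients do not matter to power.** This stands. The larger figure yields slightly more than is needed.

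**The country list shows no under-recruitment.** A reader might infer from 2875 and 1725 that the study, as allocated, cannot reach 1833. The text does not support that. It counts 14 countries, so two are missing from the list, and it allows for more. Two countries supplying 180 to 200 patients would average 90 to 100 each, well inside the listed range of 60 to 620. The country numbers are described as anticipated, and the abstract describes a fixed recruitment period that takes all eligible patients. This objection stands in full.

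**Power against harm is lower still.** A reader might also add that power is only about 67% at 1833 if IDet is worse (88.3% against 91.8%). That arises at the full planned number, so it concerns the effect assumption and not enrolment or country counts. It carries no weight here.

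**Conclusion.** The inconsistencies are real and stand in the current text. Enrolment is 3055 in one place and 3075 in three, and the stated derivation reproduces 3055 exactly. The listed countries number 12 and sum to 2875, against stated counts of 14 and seven, so 180 to 200 patients have no listed source. The abstract ties the power to the wrong number.

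The consequence for the study is small. The 20-patient difference is 0.65% and does not harm power. The 1725 figure holds only if nobody is enrolled outside the 12 listed countries and the assessable share is exactly 60%. Even then the cost is about 2.5 points of power for 95.3% on IDet against 91.8%, and power stays just above 80% with the percentages reversed. It describes what the list as printed would deliver and is not a demonstrated shortfall.

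**What to change.** 1. State one enrolment figure throughout: either 3055, which matches the derivation, or 3075 with its 1845 assessable pregnancies shown or its margin over 3055 explained.
2. Use one country count in the abstract and in Study organisation.
3. Make the country list sum to the chosen enrolment figure by adding the unlisted countries and their anticipated numbers. If they cannot be given, restate the expected assessable number (1725 from the listed countries at 60%) with its power.
4. In the abstract, attach the 80% power to the 1833 assessable pregnancies and give the enrolment figure separately as that number inflated for losses.

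The cost is a correction of text and country numbers. The design does not change, and no patients are needed beyond the stated plan.
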